### Blinding

The automated randomisation of participants after baseline completion will enable the enrolling researcher to remain blind to participant condition over the course of the trial. Those who administer the 6-month SCID interview, and who analyse the data will also remain blind to condition. The active nature of the control condition may also allow us to blind participants to condition. Participants will be informed that the purpose of the study is to investigate the efficacy of two online programs to prevent postnatal depression. However, they will not be explicitly advised of the content or intention of either site. This minor deception was designed to yield a double-blind trial of the psychological intervention. To this end, the Human Research Ethics Committees of ACT Health and the Australian National University have approved the procedure. To assess the success of blinding, participants will asked to indicate whether they were assigned to the condition that we anticipated to be more successful or the condition we expected to be less successful. This assessment will be performed immediately post-intervention.

### Analysis

The outcome variables will be analysed on an intent-to-treat (ITT) basis using a linear mixed models analysis, a procedure which is able to handle missing data [43] with timepoints as a within groups factor and intervention condition as a between groups factor. A significance level of 0.05 will be used for all outcome variables. We plan to analyse contrasts between intervention and control groups at post intervention, 3-months, 6-months and 12-months follow-up.

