**Methods/Design:**

The proposed study is a two-arm double blind randomised controlled trial. 175 participants will be recruited in the immediate postnatal period at an Australian community hospital. Women who meet inclusion criteria (internet access, email address, telephone number, over 18, live birth, fluent English) will complete the Edinburgh Postnatal Depression Scale (EPDS). Those with a score above 9 will undertake the Structured Clinical Interview for DSM Disorders (SCID). Those with a clinical diagnosis of depression, or a lifetime diagnosis of bipolar disorder or psychosis on the SCID will be excluded. Following completion of the baseline battery women will be randomised using a computer-generated algorithm to either the intervention or control condition. The intervention will consist of 5 modules of automated, interactive cognitive behaviour training (CB training), completed weekly with email reminders. The control will replicate the level of contact participants experience with the intervention, but the content will be of a general health nature. Participants will complete questionnaires immediately post-intervention (6 weeks) and 3-, 6- and 12 months follow-up. There will also be a second SCID delivered via telephone at 6 months. We hypothesise that relative to the control group, the intervention group will show a greater reduction in postnatal distress on the EPDS (primary outcome measure). We also hypothesise that the intervention group will demonstrate lower levels of anxiety and stress and higher levels of parenting confidence than the control group following intervention and/or follow-up.

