### Measures

The primary outcome will be postnatal distress. The secondary outcomes will be the severity of depressive and anxiety symptomatology, parenting confidence and diagnostic status. These will be measured as follows:

1. *Postnatal distress* will be measured online using the Edinburgh Postnatal Depression Scale (EPDS) [25]. The most widely-used measure of postnatal depression and anxiety, this instrument contains 10 items and takes around 5 minutes to complete. Answers are scored between 0 and 3, and summed for a total score (range 0 to 30) with higher scores indicating higher levels of postnatal distress. The validity of the EPDS has been established within the Australian population [26], for online administration [27] and for use in the immediate postpartum period to predict PND outcomes e.g. [28,29]. The cut-off used in this study (over 9) is that recommended by Matthey *et al.*[30] for probable minor depression.

Secondary outcomes

2. *Depressive and anxiety symptomatology* will be measured online using the Depression, Anxiety and Stress Scale (DASS) [31], a 21 item self-report questionnaire designed to measure the severity of symptoms. This self-report measure has adequate psychometric characteristics [32] and has been previously used in this population [33].

3. *Parenting confidence* will be assessed using the 15-item self-report Karitane Parenting Confidence Scale (KPCS) [34]. Although the KPCS is a new measure, it shows good test-retest reliability and internal consistency. The scale was developed and tested in Australia, making this a particularly appropriate instrument for the current study. The KPCS will be delivered via the Internet.

4. *Depression Status* will be evaluated using the Structured Clinical Interview for DSM Disorders (SCID) Module A (Mood Episodes). The SCID is a structured interview for current and past diagnoses of DSM-IV disorders. There have been a number of reliability studies yielding an acceptable range of Kappa values for the diagnosis of major depression (from 0.61 [35] to 0.93 [36]). At baseline this interview will be delivered face-to-face; however, at 6-months follow-up it will completed via telephone [37].

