### Sample size

Based on power calculations, an estimated minimum of 112 participants are required. Assuming a correlation of .5 between baseline and endpoint outcome measures, a 20% dropout, and an effect size of 0.43 [10], this sample size will have the power at 80% to detect differences at endpoint of .54 standard deviations (alpha = 0.05, non-directional test). Approximately 3000 babies are born per year at The Canberra Hospital. 20% of their mothers will score over 9 on the EPDS immediately after birth [33,41], yielding a potential pool of 600 women per year. Of these women, roughly 4% [42] will be clinically depressed and therefore excluded, leaving a potential pool of 576. Based on rates of recruitment from community samples, we anticipate that 25% of these potential participants will agree to participate in the study, yielding a sample of 144 women per year. Allowing for a further 10-20% unexpected drop-out after recruitment and before randomisation this should be sufficient to reach the target sample size of 112 participants.

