### Procedure

Ethical approval has been obtained from ACT Health Human Research Ethics Committee and The Australian National University Human Research Ethics Committee.

Women will be approached by a member of the research team while in hospital who will explain the study and offer information sheets and consent forms where appropriate. Those who consent to participate will be administered an inclusion/ exclusion criteria questionnaire by the enrolling researcher. Women who satisfy these criteria will be assessed using the Edinburgh Postnatal Depression Scale (EPDS), self-administered on a notebook computer. Women who score under 9 will not be eligible. Those who score 9 or over will then be assessed for depressive disorders, bipolar disorder or history of psychosis using a face-to-face administration of the Structured Clinical Interview for DSM Disorders (SCID). Women who have a diagnosis will be excluded from the study, as will those who scored under 9 on the EPDS.

Participants will then complete the baseline questionnaires online using a notebook computer, after which they will be randomised either to the intervention or control condition (Figure 1). After 1 week, participants will receive an email informing them that the first online module is available. They will then complete either the MoodGYM or HealthWatch modules weekly for 5 weeks.

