**Figure 1 F1:**
[figure not shown]
Study flowchart.

All participants will be invited to complete online follow-up questionnaires immediately post-intervention (6 weeks) and at 3 months, 6 months, and 12 months post-randomisation (Table 1). The 6 month SCID will be completed via telephone. Participants who develop a clinical diagnosis in the course of the trial, or contact trial staff with concerns about their wellbeing, will be referred to an appropriate health professional.

**Table 1 T1:** Schedule of questionnaires

**Instrument/ question**	**Baseline**	**6 wks**	**3 m**	**6 m**	**12 m**
Inclusion criteria questionnaire	✓	**-**	**-**	**-**	**-**
Edinburgh Postnatal Depression Scale (EPDS)	✓	✓	✓	✓	✓
Depression Anxiety and Stress Scale (DASS)	✓	✓	✓	✓	✓
Karitane Parenting Confidence Scale (KPCS)	✓	✓	✓	✓	✓
Structured Clinical Interview for DSM Disorders (SCID)	✓	-	-	✓	-
Health of infant	✓	✓	✓	✓	✓
Infant feeding status and satisfaction	✓	✓	✓	✓	✓
Level of support (MSSS)	✓	✓	✓	✓	✓
Major life events	✓	**-**	**-**	✓	✓
PND/ Depression literacy	✓	**-**	**-**	**-**	✓
Have you sought help for PND	-	✓	**-**	✓	✓
Personal details and contact information	✓	**-**	**-**	**-**	**-**
SES: age, marital status, education, occupation, income	✓	**-**	**-**	**-**	**-**
Family history of depression	✓	**-**	**-**	**-**	**-**
Personal history of depression	✓	**-**	**-**	**-**	**-**
Personal history of abuse	✓	**-**	**-**	**-**	**-**
Parity	✓	**-**	**-**	**-**	**-**
Stressfulness of pregnancy	✓	**-**	**-**	**-**	**-**
Difficulty of delivery	✓	**-**	**-**	**-**	**-**
Sex of infant	✓	**-**	**-**	**-**	**-**

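### For 6-month diagnostic status, the mixed model's missing-data claim does not hold: with a constant baseline and one follow-up SCID, it gives a completers-only contrast

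*Protocol article*

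**What the plan says.** The Measures section makes the EPDS the primary outcome and then lists the others: "The secondary outcomes will be the severity of depressive and anxiety symptomatology, parenting confidence and diagnostic status". Diagnostic status is assessed with the SCID mood module.

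The Analysis section gives one method for all outcome variables. It is intent-to-treat, "using a linear mixed models analysis, a procedure which is able to handle missing data", with time as a within-groups factor, condition as a between-groups factor, and contrasts at each of the four follow-ups. No outcome is excepted and no other approach to missing data is named.

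Table 1 schedules the EPDS, DASS and KPCS at all five time points, but the SCID only at baseline and 6 months. On the follow-up interview, the Procedure section says: "The 6 month SCID will be completed via telephone". On the baseline interview it says: "Women who have a diagnosis will be excluded from the study".

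The only dropout figure for randomised women is in the Sample size section: "Assuming a correlation of .5 between baseline and endpoint outcome measures, a 20% dropout, and an effect size of 0.43". It is attached to an unnamed endpoint, not to the SCID.

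**The concern.** A linear mixed model makes use of incompletely followed women because their observed values of an outcome are correlated with the missing ones. That argument is sound for a scale measured at baseline and four follow-ups. It needs at least one other measurement of the same outcome that varies between women. The SCID has none: the baseline value is fixed by the entry criteria, and there is only one value after it.

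If so, a result for diagnostic status could be reported as intent-to-treat with missing data handled when it is a comparison of women who completed the telephone interview. The Discussion states the trial's aim as primary prevention of postnatal depression, and the SCID is the only diagnostic measure of that. Replacing the linear model with a logistic one on the same data would fix the mismatch with a yes/no outcome, but it would still leave these women out.

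**Working it through.** **1. What the model can recover.** Within one arm, let y0 be baseline status and y1 the 6-month status, with y1 missing for some women. With a separate mean for each arm and time, the likelihood-based estimate of the 6-month mean is

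estimate = mean(y1 among completers) − b × [mean(y0 among completers) − mean(y0 among all)],

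where b is the slope of y1 on y0 implied by the fitted covariance. The second term is the whole missing-data correction. Every randomised woman is free of current depression at baseline, so y0 = 0 for all, the bracket is 0 − 0 = 0, and the correction vanishes whatever b is. The arm difference is then exactly the completers' difference.

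**2. Numerical check.** In simulated data for 20,000 women, status at 6 months and a 6-week symptom score shared a common cause. Loss depended on the 6-week score, in opposite directions in the two arms, with 18.6% and 18.5% missing.

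| Analysis | Risk difference (points) |
|---|---|
| All women, no loss | −2.7 |
| Completers only | −5.6 |
| Linear mixed model on SCID status | −5.6 |

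The last two agree to more than six decimals. The size of the gap from −2.7 is a product of the assumed loss mechanism; the identity is not.

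**3. The plan's sample size.** The Sample size section gives 112 for 80% power, a difference of 0.54 SD and two-sided alpha of 0.05. Assuming equal arms and unit SD, n per arm = 2 × (1.960 + 0.842)² / 0.54² = 53.8, so 108 in total; the t-based version gives 55 per arm, or 110. With 0.43/0.8 = 0.5375 in place of 0.54, the t-based version gives 56 per arm, or 112. So 112 is reproduced only as a number analysed, although the section ends by treating it as the number left after pre-randomisation loss. Both readings, and the Abstract's 175, are shown below.

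**4. How many diagnoses could be missing.** Assumptions: the 20% planning dropout applies to the 6-month SCID, and 13% of women are cases (the Background's prevalence, used here as an assumed event rate in both arms).

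| Randomised | Missing at 20% | Cases at 13% |
|---|---|---|
| 112 | 112 × 0.20 = 22.4 | 112 × 0.13 = 14.6 |
| 140 (= 112/0.8) | 140 × 0.20 = 28.0 | 140 × 0.13 = 18.2 |
| 175 | 175 × 0.20 = 35.0 | 175 × 0.13 = 22.8 |

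For 112 women, loss of 10% to 40% gives 11.2 to 44.8 missing. Missing results outnumber cases whenever the loss rate exceeds the event rate: true at 20% against 13%, not at 10% against 13%.

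**5. Extreme bounds.** Take 56 per arm, 11 missing and 45 seen in each, and 13% observed in both. If all missing women in one arm and none in the other were cases, the difference would be ±11/56 = ±19.6 points around zero. These are limits, not expected values.

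**The case against.** **Silence is not a defect.** A missing-data rule for one secondary outcome is commonly left to a statistical analysis plan, and none is shown. This is right as far as it goes: the missing rule alone would be no finding. What remains is that the article positively assigns all outcome variables to a method and credits it with a property it lacks for one of them.

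**Loose wording.** The Analysis section describes contrasts at four follow-ups, which only the EPDS, DASS and KPCS have, so the authors may have had just those scales in mind. That is plausible, and the correction is then a clarification. But diagnostic status is a listed outcome, and no other method is given for it.

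**Stronger readings the documents do not support:**

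- *The plan expects to lose 20% of the 6-month SCIDs.* The 20% belongs to the power calculation and names neither time point nor instrument. The interview is by telephone, separate from the online questionnaires, and a telephone number is an entry condition. Its loss could be lower or higher.
- *Women who miss the interview cannot be scored.* The SCID covers current and past diagnoses, so a late interview could help, and the repeated EPDS and DASS scores carry information. The stated model uses neither.
- *The result will be biased in a known direction.* That needs a loss mechanism the article does not give. For illustration, assume true rates of 20% v 10%, a correlation of 0.7 between interim symptoms and 6-month status, odds of loss multiplied by 2.2 per SD of symptoms, and 20% loss. The 10-point difference becomes 8.9 if loss depends on symptoms in both arms, and about 7 or 12 if in one arm only. With 45 completers per arm at 16.8% v 7.9%, the standard error is √(0.168 × 0.832/45 + 0.079 × 0.921/45) = 6.9 points, a 95% half-width of about 13.5. All these shifts lie within sampling error.
- *The trial's main conclusion is at risk.* The primary outcome is the EPDS, and none of the hypotheses in the Abstract or Discussion concerns SCID diagnosis.

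**Conclusion.** The point holds in limited form. For 6-month diagnostic status, the intent-to-treat and missing-data statement in the Analysis section is wrong: the model reduces exactly to a completers-only contrast. This follows from the assessment schedule and the baseline exclusion and needs no assumption about why women are lost. The statement stands for the EPDS, DASS and KPCS.

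The practical size is uncertain. About 22 missing results against about 15 cases among 112 women rests on two assumptions, 20% loss and a 13% event rate, neither of which the article states for this outcome. The direction and size of any bias cannot be derived from the document.

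Severity is moderate to minor: a secondary outcome is affected, though the one closest to the prevention aim.

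**What to change.** In the Analysis section, limit the missing-data statement to the EPDS, DASS and KPCS. For 6-month diagnostic status:

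- Name a method for a binary outcome and apply it to all randomised women.
- Fill missing diagnoses by multiple imputation from a small model: arm plus one or two summaries of the available EPDS or DASS scores nearest to 6 months. With about 45 women seen per arm at 13%, there would be about 6 events per arm (45 × 0.13 = 5.9), so entering every scheduled score and risk factor would make the model unstable.
- Report completers-only and missing-as-depressed results as sensitivity analyses. The latter is severe: with 11 of 56 missing, an observed 13% becomes (5.85 + 11)/56 = 30%. It should be read as a bound.

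The cost is a few sentences, a little more analysis work and no new data collection. The downsides are some dependence on the imputation model, especially for women who also lack questionnaires near 6 months, and possibly a wider interval.

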## Methods/Design

### Design

A 2 (Condition) X 4 (Time) double blind, randomised controlled design is planned. Participants will be randomly allocated to either the online intervention or an online control condition. Outcomes will be assessed at baseline, post-intervention (6 weeks), 3 months, 6 months, and 12 months post-randomisation.

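### The primary model names no baseline EPDS term and the 2 × 4 label conflicts with five assessments; fixing a baseline adjustment would add power at no cost

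*Protocol article*

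**What the plan says.** Three sections of the protocol article bear on the role of baseline EPDS.

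- **Analysis.** The outcomes go into an intention-to-treat linear mixed model "with timepoints as a within groups factor and intervention condition as a between groups factor". The planned comparisons are between arms at 6 weeks, 3, 6 and 12 months. No covariate is named, and the section does not say whether baseline counts as one of the timepoints.
- **Design.** "A 2 (Condition) X 4 (Time) double blind, randomised controlled design is planned". The same paragraph then says: "Outcomes will be assessed at baseline, post-intervention (6 weeks), 3 months, 6 months, and 12 months post-randomisation". That is five occasions, and Table 1 also shows the EPDS at five.
- **Sample size.** "Assuming a correlation of .5 between baseline and endpoint outcome measures", together with 20% dropout, the section states that "this sample size will have the power at 80% to detect differences at endpoint of .54 standard deviations" ("alpha = 0.05, non-directional test"), for a minimum of 112 participants.

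The Abstract and Discussion state the primary hypothesis as a larger fall in EPDS in the intervention arm.

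**The concern.** The sample-size section brings in a baseline–endpoint correlation, but the analysis section has no term through which that correlation would act. The label 2 × 4 fits a model of the four follow-ups, with baseline either a covariate or left out. The list of five assessments fits a model with baseline as a level of time. These are different estimators with different precision, and the text does not choose between them.

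What is at stake is precision. Baseline EPDS is collected from every participant before randomisation, and the article itself assumes that it correlates .5 with the endpoint. In a trial of 112, an analysis that leaves it out gives up power that costs nothing to keep. An open choice between raw, change and adjusted contrasts for the primary outcome also leaves room to choose after the results are seen.

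**Working it through.** **Inputs.** From Sample size: two-sided alpha 0.05, 80% power, detectable difference 0.54 SD, r = .5, dropout 20%, cited effect 0.43, N = 112. Assumed: 1:1 allocation (the ratio is not stated), and equal SDs at baseline and follow-up for the change-score factor.

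**Variance factor v of the arm contrast at one visit, relative to the raw follow-up difference**

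- Follow-up score alone: v = 1. With complete data this also covers a follow-up contrast from a five-level model with unconstrained baseline means.
- Change from baseline: v = 2(1 − r) = 2(1 − .5) = 1.
- Baseline as covariate, or arm means constrained equal at baseline: v = 1 − r² = 1 − .25 = 0.75.

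**Step 1: reproduce 112.** N = 2 × 2v(1.960 + 0.842)²/d², with the number per arm rounded up.

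| d | v | Dropout inflation | N (normal) | N (t) |
|---|---|---|---|---|
| 0.43/0.8 = 0.5375 | 1 | none | 110 | 112 |
| 0.54 | 1 | none | 108 | 110 |
| 0.54 | 0.75 | none | 82 | 84 |
| 0.54 | 0.75 | ÷ 0.8 | 103 | 105 |

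The stated 112 comes out with v = 1 and no inflation for dropout. An adjusted calculation with 20% dropout would give 103 to 105. So 112 does not rest on a precision gain from r.

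**Step 2: power at 112 randomised with 20% dropout.** Completers per arm: m = 112 × 0.8/2 = 44.8. Power = Φ(δ/√(2v/m) − 1.960), with √(2/44.8) = 0.2113.

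- v = 1: 0.54/0.2113 = 2.556. Φ(0.596) = 72.4% (71.5% with the t distribution).
- v = 0.75: 2.556/0.866 = 2.951. Φ(0.991) = 83.9% (83.1% with t).

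The difference detectable with 80% power is 2.802 × 0.2113 = 0.592 SD at v = 1, and 0.592 × 0.866 = 0.513 SD at v = 0.75.

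**Step 3: sensitivity to r.** For r from .3 to .7, adjusted power at 0.54 SD runs from 76% to 95%, against 72% unadjusted.

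Selection on the EPDS may lower r. The Sample size section expects 20% of mothers to score over 9. Suppose scores are normal and .5 is the correlation before selection.

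- The top 20% starts at z = 0.842 and has mean 0.280/0.20 = 1.400.
- The variance left is 1 + 0.842 × 1.400 − 1.400² = 0.219, so the SD ratio is 0.468.
- The correlation after selection is .5 × 0.468/√(0.75 + 0.25 × 0.219) = 0.234/0.897 = 0.26.
- Then v = 1 − 0.26² = 0.932, and power = Φ(2.556/0.966 − 1.960) = Φ(0.687) = 75%.

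**Step 4: the other sample size.** The Abstract gives 175 participants. With 20% dropout that is 70 per arm, and power for 0.54 SD is 89% unadjusted and 96% adjusted at r = .5. The conflict between 112 and 175 is a separate matter.

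**The case against.** The strongest reply is that the article never rules baseline adjustment out. Three sentences of analysis text in a condensed article need not list covariates, and both the assumed correlation and the hypothesis of a larger fall suggest that baseline was meant to enter somehow. This stands in part. A reader might infer that the trial will not adjust for baseline, and the document does not support that. It supports only that no adjustment is specified and that 2 × 4 disagrees with the list of assessments.

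Three further inferences are tempting and should not be drawn.

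- *That the sample size relied on a gain from r which the analysis then forgoes.* Step 1 shows otherwise: 112 reproduces at v = 1. At r = .5 a change-score analysis also has factor 1, so r may even have been used, without effect. The unadjusted shortfall to 72% arises because 112 was not inflated for dropout, which is a different issue.
- *That the hypothesis is not tested.* Under randomisation the expected baseline means are equal, so the arm difference at follow-up and the arm difference in change have the same expectation.
- *That chance baseline imbalance under unstratified randomisation biases the result.* An unadjusted randomised comparison is unbiased. Chance imbalance is already part of its standard error, so counting it beside the precision loss would count one cost twice.

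A likelihood-based model with baseline as a time level does use baseline to inform missing follow-ups, so the loss under that reading is slightly smaller than complete-data arithmetic suggests. The headline gain is also the favourable case. If selection brings r down to 0.26, it is about 3 points of power, not 12.

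**Conclusion.** The point holds as one of unfixed specification and avoidable loss of efficiency. As written, the model contains time and condition only, the role of baseline EPDS is left open by the conflict between 2 × 4 and five assessments, and r = .5 is linked to no model term. The planned contrasts are valid. Adjustment would raise power for 0.54 SD at 112 randomised from about 72% to 84% at r = .5, or to about 75% at r = 0.26.

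These figures rest on 1:1 allocation, 20% dropout, a single-visit contrast among completers, and for the lower value normal scores with .5 as the correlation before selection. The gain is positive for any r other than zero. It is a free improvement, and the plan would not be unsound without it.

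**What to change.** - In Analysis, specify the primary model as a mixed model for the four post-baseline EPDS scores with condition, time, condition × time, baseline EPDS and baseline × time. A five-occasion model with arm means constrained equal at baseline is an alternative. Adding baseline as an unconstrained fifth level would not bring the gain.
- Use the same form for DASS and KPCS, each with its own baseline.
- In Design, reconcile 2 × 4 with the five assessments: four follow-up levels with baseline as covariate, or 2 × 5.
- In Sample size, say which model term the correlation of .5 refers to, and whether it is meant for the selected sample.

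The cost is wording only. Table 1 already schedules the EPDS, DASS and KPCS at baseline, and the Procedure section has the baseline battery completed before randomisation.

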## Discussion

The aim of this trial is to assess the effectiveness of online CB Training for the primary prevention of postnatal depression in an at-risk sample. To our knowledge there are no published studies investigating the use of an online intervention to prevent PND.

We hypothesise that the MoodGYM prevention group will show a greater reduction in postnatal distress as measured by the EPDS. We also hypothesise that they will demonstrate lower levels of anxiety and stress and higher levels of parenting confidence than the control group.

The current study addresses many of the shortcomings of earlier trials. Many trials targeted “at-risk” women, but failed to screen out women with a current disorder. By contrast, the current study excludes women with a diagnosis of depression and thus is a true prevention trial not contaminated by treatment effects which inflate the effect size. Most previous PND prevention trials have used interventions that been previously untested either as *treatments* for PND or as treatments or preventive interventions for depression in general. Therefore the significance of a failure of the intervention to prevent PND is difficult to interpret. MoodGYM is an intervention of demonstrated efficacy both as a treatment, and as prevention for depression in a range of non-PND populations. Similarly, many of the studies using CBT incorporate additional interventions in the prevention program. Again, this complicates the interpretation of the study findings. We propose to use CB Training by itself rather than as part of a multi-component intervention. This will allow us to draw conclusions about the utility of Cognitive Behavioural strategies specifically for PND prevention.

The major limitation of the study is its small geographic coverage. For pragmatic reasons, the study will not, at this stage, be conducted in more than one site. The recruited sample may therefore not be representative of the broader population. Canberra’s population is better educated and of higher socio-economic status than the average for Australia. Further, since there have been no previous studies of online CB Training interventions for this population the recruitment rate is difficult to predict with certainty. A further potential limitation of the intervention is that it is not tailored to PND specifically. On the other hand, it possible that a generic intervention could have a normalising effect on symptoms.

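### The primary outcome (EPDS) has no primary assessment time: the sample size serves one comparison at an unidentified endpoint, while the analysis lists four unranked contrasts at 0.05

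*Protocol article*

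**What the plan says.** In Methods/Design, the Measures section states "The primary outcome will be postnatal distress" and assigns the EPDS to it, without a time. The hypothesis in the Discussion, "We hypothesise that the MoodGYM prevention group will show a greater reduction in postnatal distress as measured by the EPDS", gives no time either, and neither does its counterpart in the Abstract.

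The Design section sets four assessments after baseline: "Outcomes will be assessed at baseline, post-intervention (6 weeks), 3 months, 6 months, and 12 months post-randomisation". Table 1 collects the EPDS at every one of them.

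The Sample size section claims 80% power with 112 participants "to detect differences at endpoint of .54 standard deviations", at a two-sided alpha of 0.05. It does not say which assessment the endpoint is.

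The Analysis section specifies a linear mixed model with time as the within factor and condition as the between factor. It continues "A significance level of 0.05 will be used for all outcome variables" and then "We plan to analyse contrasts between intervention and control groups at post intervention, 3-months, 6-months and 12-months follow-up". The four contrasts are not ranked, and no overall test is made a condition for looking at them.

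**The concern.** Sample size and Analysis do not fit together. One section plans a single test at a single time; the other lists four contrasts on the same outcome and does not say which of them the power calculation was for. Someone following the article could present whichever EPDS contrast turned out significant as the primary result, and nothing in the text would forbid it. Two things are at stake: the false-positive rate of the main efficacy claim, and whether the time that supports the claim was chosen before or after the data were seen.

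This goes beyond detail that an article leaves to a fuller document. The assessment time is part of what defines the primary outcome, and the article has already fixed four contrasts and one blanket significance level around that gap.

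**Working it through.** **Step 1. Reproduce the 112.** Inputs from Sample size: effect size 0.43, 20% dropout, detectable difference 0.54 SD, 80% power, two-sided alpha 0.05, correlation 0.5. Allocation of 1:1 is assumed, as no ratio is stated.

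- 0.43 / 0.8 = 0.5375, which rounds to the stated 0.54. The article does not show this step; it is inferred because it fits.
- The normal approximation is n per arm = 2(1.960 + 0.842)² / d². With d = 0.5375 this gives 54.3, so 55 per arm and 110 in total.
- The two-sample t-test gives 55.3, so 56 per arm and **112** in total. With d = 0.54 it gives 55 per arm, 110 in total.
- The SD is taken as 1. That is also the SD of a change score at correlation 0.5, since √(2(1 − 0.5)) = 1.

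The 112 is therefore what one two-sample comparison at one time needs. It contains no allowance for four tests.

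**Step 2. False-positive chance if any one of four contrasts counts.** Assume no effect at any time, four two-sided tests at 0.05 (critical value c = 1.96) and an equal correlation ρ between the test statistics.

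- Independent contrasts: 1 − 0.95⁴ = 1 − 0.8145 = 18.5%.
- Correlated contrasts: 1 − ∫ φ(u) [Φ((c − √ρ·u)/√(1 − ρ)) − Φ((−c − √ρ·u)/√(1 − ρ))]⁴ du.

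| ρ between times | Chance of at least one p < 0.05 |
|---|---|
| 0 | 18.5% |
| 0.5 | 15.6% |
| 0.6 | 14.4% |
| 0.7 | 13.0% |
| 0.8 | 11.4% |
| 0.9 | 9.4% |

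If the correlation instead falls with distance in time (AR(1), simulated), a lag-1 correlation of 0.5 gives 16.6% and 0.8 gives 12.6%, inside the same range.

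**Step 3. Which ρ applies?** The article gives 0.5 between baseline and endpoint only. Suppose 0.5 held for every pair of times. Raw or change-score contrasts would then have ρ = 0.5, hence 15.6%. Baseline-adjusted contrasts would have ρ = (0.5 − 0.25)/(1 − 0.25) = 0.33, hence about 17%. The article does not say that 0.5 applies between follow-up times, so the range is the honest answer.

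**Step 4. What the remedies cost.** Power for 0.54 SD with 56 per arm is Φ(0.54·√28 − critical value), where 0.54·√28 = 2.857.

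- One contrast at 0.05: Φ(2.857 − 1.960) = 81.5%.
- Bonferroni over four, 0.0125 each: Φ(2.857 − 2.498) = 64.0%.

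Naming one primary time keeps the first figure. Splitting alpha equally over four times gives the second.

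**The case against.** The strongest objection is that no any-of-four rule is written down. The 0.05 is stated per outcome variable, not per contrast. The Design section describes a condition-by-time layout and the hypothesis is about a greater reduction, which fits one overall condition or condition-by-time test with the four contrasts describing its pattern. Such a test, if primary, would hold 5% when there is no effect at any time. This stands in part: the 9% to 18% is conditional on a reading and is not a rate that the plan commits to. But the overall test is not named as primary either, and the power calculation matches a single-time comparison, not an interaction test.

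A second objection is that the multiplicity rules may be in a full protocol or analysis plan that is not shown. That is possible, and the absence of an adjustment alone would not be a finding. The mismatch between one powered endpoint and four equal-ranking contrasts is in the article itself.

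Three stronger readings are tempting, and the document does not support them:

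- A reader might take the Abstract's phrase "higher levels of parenting confidence than the control group following intervention and/or follow-up" as the success rule. It belongs to the sentence on anxiety, stress and parenting confidence, which are secondary. The EPDS sentence before it has no such wording.
- A reader might conclude that the 80% power fits no test. Step 1 shows that it fits any single-time contrast at 0.05. What is missing is which one.
- A reader might argue for 6 months because "Participants who develop a clinical diagnosis in the course of the trial, or contact trial staff with concerns about their wellbeing, will be referred", so that referral after the 6-month SCID could narrow the 12-month difference. That would affect power, not type I error, and no size can be given. Referral after a woman contacts staff can also happen earlier, and the order of the 6-month EPDS and interview is not stated. The article gives no basis for preferring one time.

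**Conclusion.** The point holds in this form: the time at which the primary outcome is judged is not identified, and the powered endpoint cannot be matched to one of the four planned contrasts. If any one significant EPDS contrast is taken as success, the false-positive chance is about 9% to 18%, roughly two to nearly four times the nominal 5%. This assumes no effect at any time, four two-sided tests at 0.05, and between-time correlations from 0.9 down to zero. A single figure such as 15.6% needs a correlation that the article does not supply. If one overall test or one named time governs the primary claim in a document not shown, the inflation disappears, but the article would still need to say so.

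**What to change.** In the Analysis section, name one primary test before outcome data are seen: the between-group EPDS contrast at one stated assessment, taken from the mixed model, at two-sided 0.05. The sponsor should choose the time and give the reason. Label the other three EPDS contrasts secondary, handled by a fixed sequence, by Holm, or as estimates with confidence intervals only. In the Sample size section, state that the endpoint is the chosen assessment, and make the primary hypothesis name the same time.

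The cost is a few sentences. Alpha stays at 0.05 and the required 112 does not change. The small downside is that an effect seen only at another time can no longer be claimed as the primary result.
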